**Figure 3 figure3:**
[figure not shown]
Inclusion criteria and postoperative outcomes of enrolled extended criteria donor (ECD) liver and kidney recipients.

#### Kidney Transplant Primary Outcome

The incidence and timing of DGF will be evaluated and correlated with the outcomes of the kidney recipients (Figure 3). DGF is defined as the need for renal replacement therapy during the first week posttransplant [18]. The length of renal replacement therapy is calculated as the interval between the first day and last day of dialysis.

#### Liver Transplant Secondary Outcomes

Secondary outcome measures in the LT groups are the incidence of PNF, defined as patient death or the need for early retransplantation within the first 7 postoperative days, excluding acute vascular complications [18]; postreperfusion syndrome rate; length of hospital stay (LHS); liver function test values (ie, bilirubin, AST, ALT, and gamma glutamyl transferase) at discharge and 1, 3, and 6 months after LT; occurrence of acute rejection events, biliary complications, portal vein thrombosis, or hepatic artery thrombosis within 6 months from the transplant; graft survival, defined as the time from transplant to retransplant or patient death due to liver failure; and patient survival.

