## Methods

### Study Design

In an open-label, single-center, randomized clinical trial, we will compare HOPE (study group) to SCS (control group) in ECD KT and LT. In the HOPE group, 55 livers and 55 kidneys will be preserved by SCS at 4-10°C from the end of organ retrieval until arrival at the transplant hospital. Afterwards, grafts are preserved with HOPE at 4-10°C for a minimum of 1 hour for livers and 2 hours for kidneys until implantation in the recipient. HOPE starts during back-table graft preparation. During the back-table procedure, organs are flushed with a preservation fluid (Belzer solution). Then, the organ is perfused with HOPE through a closed recirculating system.

In the SCS group, 55 livers and 55 kidneys will be preserved by SCS at 4-10°C from the end of the organ retrieval until implantation in the recipient.

In this study, 220 patients will be enrolled, with 55 in each of the following groups: LT-HOPE, LT-SCS, KT-HOPE, and KT-SCS.

The trial design is outlined in Table 1, and the protocol algorithm is shown in Figure 1.

Based on the number of transplants usually performed at the participating center, this clinical study is estimated to be accomplished in 2 years, including 12 months of patient enrollment and 12 months of follow-up. Enrollment at the Bologna Transplant Center started in January 2019 and will end in January 2020 (Figure 2).

**Table 1 table1:** Trial design to evaluate the benefit of end-ischemic hypothermic oxygenated perfusion (HOPE) on extended criteria donor grafts for livers and kidneys as compared with static cold storage (SCS), N=220.

			Study group (HOPE)		Control group (SCS)
Number of livers			55		55
Number of kidneys			55		55

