### Analyses of Outcomes

#### Liver Transplant Primary Outcome

The rate of EAD and the Liver Graft Assessment Following Transplantation (L-GrAFT) risk score [16,17] will be analyzed to evaluate the postoperative outcomes of the enrolled liver recipients (Figure 3).

EAD is defined by the presence of at least one of the following lab results: bilirubin >10 mg/dL, international normalized ratio >1.6 on postoperative day 7, ALT >2,000 IU/mL within the first 7 postoperative days, or AST >2,000 IU/mL within the first 7 postoperative days [17]. The L-GrAFT risk score is calculated from the peak AST level, bilirubin levels, platelet counts, and international normalized ratio values from days 1 to 10 post-LT [17].

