#### Kidney Transplant Secondary Outcomes

Secondary outcomes for kidney recipients are the incidence of PNF, defined as irreversible graft dysfunction with graft loss, which can also be due to rejection or vascular thrombosis; postreperfusion syndrome rate; number of dialyses required in the posttransplant follow-up; LHS; renal function, as measured using creatinine level and estimated glomerular filtration rate, at discharge, 1, 3, and 6 months posttransplant; occurrence of acute rejection events, anastomotic or nonanastomotic ureteral stenosis, or vascular thrombosis within 6 months from the transplant; graft survival, defined as the time from transplant to graft loss or return to dialysis; and patient survival.

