### Statistical Analyses

#### Sample Size Calculation

The sample size was calculated using the primary outcomes of EAD and DGF for LT and KT, respectively, and the secondary outcomes of PNF and LHS, as reported in similar studies [11,19,20].

In particular, the rates of PNF and EAD are expected to decrease for the LT-HOPE group, thereby improving the postoperative course and LHS. We are expecting the following reductions in these parameters: PNF, 5% (HOPE) vs 10% (SCS); EAD, 10% (HOPE) vs 20% (SCS); and postoperative LHS <21 days, 80% (HOPE) vs 50% (SCS).

In KT, HOPE should reduce the rate of DGF from 50% to 30%, with a general improvement in the postintervention outcomes.

Based on these parameters, the total sample size was estimated at 220 patients, with distribution throughout the 4 groups as already explained (alpha=.05, two-sided test, power of 80%; calculated with nQuery Advisor 7.0, Statsols, Cork, Ireland).

The sample size was calculated to account for a dropout risk of 5-10% for the year.

A preliminary analysis will be performed when half of the enrollment is completed.

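### Liver function tests are compared between arms at discharge, a day that the plan itself expects HOPE to move

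*Protocol article*

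**What the plan says.** Under Liver Transplant Secondary Outcomes, the protocol article lists bilirubin, AST, ALT and GGT "at discharge and 1, 3, and 6 months after LT". Under Kidney Transplant Secondary Outcomes, it lists creatinine and eGFR "at discharge, 1, 3, and 6 months posttransplant". Both sections also make length of hospital stay (LHS) an outcome in its own right.

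For livers, Sample Size Calculation states the expected effect on stay: "postoperative LHS <21 days, 80% (HOPE) vs 50% (SCS". For kidneys it gives a DGF figure and then only says that this comes "with a general improvement in the postintervention outcomes", with no length of stay.

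Statistical Tests compares continuous variables by ANOVA or Kruskal-Wallis, depending on their distribution. It mentions no adjustment for the day of measurement.

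Other early measures have fixed windows. EAD uses postoperative day 7 or the first 7 days, L-GrAFT uses values "from days 1 to 10 post-LT", and DGF is judged in the first week.

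**The concern.** Randomisation makes the arms comparable at a common time since transplant. Discharge is not a common time. It follows randomisation, and for livers the plan expects treatment to change it. Function tests move during early recovery, so a difference at discharge reflects both how well the graft works and how long after transplant it was measured. A one-way comparison of the two arms cannot separate these.

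The trial is open label ("In an open-label, single-center, randomized clinical trial"), so knowledge of the arm may also influence when a recipient goes home.

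At stake is the only function-test comparison before month 1 among the secondary outcomes. A reader could take it as evidence for or against early benefit when it cannot bear either reading.

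**Working it through.** **Inputs from the protocol article.** For livers, the probability of a stay under 21 days is 0.80 (HOPE) and 0.50 (SCS), from Sample Size Calculation. Group size is 55, from Study Design: "with 55 in each of the following groups: LT-HOPE, LT-SCS, KT-HOPE, and KT-SCS". The 80% and 50% are planning assumptions, so there is no derived figure to reproduce.

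**Step 1: what follows without further assumptions.** Expected numbers with the discharge test before day 21 are 0.80 × 55 = 44 (HOPE) and 0.50 × 55 = 27.5 (SCS), a gap of 30 percentage points. The SCS median is day 21, and day 21 is the 80th percentile for HOPE.

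**Step 2: gap in median sampling day.** The article gives no mean, median or spread, so a shape must be assumed. For a log-normal stay with log-SD s, the HOPE median is 21 × exp(−0.8416 × s), where 0.8416 is the 80th percentile of the standard normal. The share still in hospital at day 30 is 1 − Φ(ln(30/median)/s).

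| Assumed s | HOPE median | SCS median | Gap (days) | In hospital at day 30, HOPE | In hospital at day 30, SCS |
|---|---|---|---|---|---|
| 0.3 | 16.3 | 21 | 4.7 | 2% | 12% |
| 0.5 | 13.8 | 21 | 7.2 | 6% | 24% |
| 0.7 | 11.7 | 21 | 9.3 | 9% | 31% |

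With s = 0.8 the HOPE median is 10.7. With an exponential stay it is 9.0 (gap 12). For recipients still in hospital at day 30, the discharge test would come after the month-1 test, and more of them would be in the SCS arm.

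**Step 3: two illustrations of direction.** The half-lives are assumptions, not figures from the article.

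- *Same course in both arms, earlier discharge with HOPE.* If a marker falls towards zero with half-life h, the HOPE/SCS ratio at the median discharge day is 2^(gap/h). For h = 7 days this is 2^(4.7/7) = 1.6 to 2^(9.3/7) = 2.5. For h = 14 days it is 1.3 to 1.6. Equal grafts would look worse under HOPE.
- *Discharge when the marker reaches an acceptable level.* Both arms then show about that level at discharge, a ratio near 1. With h = 7 days, reaching it 4.7 to 9.3 days sooner means HOPE values at any common day are 1/1.6 = 0.63 to 1/2.5 = 0.40 times those of SCS. A real benefit would disappear from the discharge comparison.

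The same gap in stay therefore fits bias in either sense.

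**Step 4: kidneys.** No length-of-stay figure is given, so no gap can be computed.

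**The case against.** Several points against the concern are sound and limit it.

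- **Size and direction.** A reader might infer that HOPE discharge values will look 1.6 to 2.5 times worse. The documents do not support this. That ratio needs identical graft courses, whereas the plan expects less PNF and EAD with HOPE, "thereby improving the postoperative course and LHS": stay shortens because grafts work better. It also needs decay to zero. If half of the day-21 value were a stable baseline (an assumption), the range would be 0.5 + 0.5 × 1.6 = 1.3 to 0.5 + 0.5 × 2.5 = 1.8. It does not apply to eGFR, which does not fall in recovery. The ratios are illustrations only.
- **Kidneys.** A reader might infer that the plan expects kidney recipients to go home much earlier. It states only a general improvement. The design flaw carries over by reasoning, not by a stated figure.
- **Deaths.** Recipients who die in hospital have no discharge value, but a death before day 7 removes a fixed-day value too. This is a reason to state a rule at any time point, not a defect peculiar to discharge.
- **Scope.** Early graft function is already measured at fixed times through EAD, L-GrAFT and DGF.
- **An analysis plan not shown.** It might adjust for postoperative day or treat discharge values as descriptive. However, the article itself sets the time point, and adjusting for a day that treatment influences would not restore a clean comparison.

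None of this makes the liver discharge comparison interpretable.

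**Conclusion.** The point holds for livers on the plan's own figures: the discharge comparison samples the arms at different postoperative days. The 30-point difference at day 21 is stated in the article. The gap of roughly 5 to 9 days between medians rests on an assumed log-normal stay with log-SD 0.3 to 0.7. The sign of the resulting bias cannot be determined from the documents, so the discharge result should not be read as an effect on graft function in either direction. For creatinine and eGFR the point is inferred.

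The reach is narrow: one of four time points of one secondary outcome per organ. A reader might extend the doubt to the primary outcomes or to the later function tests, but EAD, L-GrAFT, DGF and the values at months 1, 3 and 6 are all at fixed times and are unaffected. The change is worth making because it is specific and cheap, not because the trial's main conclusion depends on it.

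**What to change.** - **Livers:** make the early between-arm comparison of bilirubin, AST, ALT and GGT at postoperative day 7. Bilirubin, AST and ALT are already needed in that window for EAD.
- **Kidneys:** compare creatinine and eGFR at one fixed early postoperative day, named in advance.
- **Both:** state how recipients who died or lost the graft before that day enter the comparison and, for kidneys, those still on dialysis. One option is to rank them worst in a rank-based test.
- **Discharge values:** keep them as descriptive data, reported with the day of discharge and without a between-arm test.
- **Months 1, 3 and 6:** leave as they are.

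**Cost.** GGT is not an input to EAD or L-GrAFT, and a fixed-day kidney value is not otherwise required, so both may need to be added. Some kidney recipients discharged early may need an outpatient sample. The change needs an approved amendment, and the article reports 108 of 220 participants already recruited. For them, the fixed-day value is available only if it was recorded in routine care.

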### Posttransplant Follow-up

Postoperative follow-up is carried out according to the local protocol. Hepatic and renal function tests and abdominal ultrasound are performed at each follow-up visit. Follow-up will end at 12 months.

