#### Statistical Tests

The continuous variables will be compared using parametric (ANOVA) or non-parametric (Kruskal-Wallis) tests according to the data distribution, and the categorical variables will be compared using chi-squared tests. Multivariate analysis will be performed using forward stepwise logistic regression analysis. Survival analysis will be conducted using the Kaplan-Meier method. *P* values <.05 will be considered statistically significant.

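### Liver graft survival counts only liver-failure deaths under Kaplan-Meier and does not fit the liver PNF rule; the kidney definition leaves the status of death unclear

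*Protocol article*

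**What the plan says.** All references are to the protocol article.

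- **Liver graft survival** (Liver Transplant Secondary Outcomes): "graft survival, defined as the time from transplant to retransplant or patient death due to liver failure". Deaths from any other cause are not events.
- **Liver PNF** (same section): "incidence of PNF, defined as patient death or the need for early retransplantation within the first 7 postoperative days, excluding acute vascular complications". The deaths counted here are not limited to liver failure.
- **Kidney graft survival** (Kidney Transplant Secondary Outcomes): "graft survival, defined as the time from transplant to graft loss or return to dialysis; and patient survival". Death is not named as a graft-survival event, and graft loss is not defined further.
- **Kidney PNF** (same section): "PNF, defined as irreversible graft dysfunction with graft loss, which can also be due to rejection or vascular thrombosis".
- **Method** (Statistical Tests): "Survival analysis will be conducted using the Kaplan-Meier method".
- **Horizon** (Posttransplant Follow-up): "Follow-up will end at 12 months".

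Patient survival is a separate secondary outcome for both organs. Study Design gives 55 recipients in each of the four groups and describes the trial as open-label.

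**The concern.** A recipient who dies with a graft that has not failed can no longer lose it. If that death is not an event, a Kaplan-Meier analysis can only censor it, which treats the recipient as still liable to graft failure at a later date. One minus Kaplan-Meier then estimates failure in a setting where nobody dies of other causes, and as a statement of actual 12-month risk it is too high.

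Two further matters are specific to liver. First, whether a death counts depends on whether someone attributes it to liver failure. The Ethical Review section says the research team learns the allocation after inclusion, and the only blinded assessment described is that of the pathologists reading tissue. Second, the same paragraph gives early death a different status under PNF.

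At stake is whether the reported graft survival can be read at all. A reader may take the unqualified term as all-cause, and one recipient could appear in the same report both as a primary non-function and as censored with a surviving graft.

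**Working it through.** The article states no graft-survival rate, event count or power, so there is no figure of its own to reproduce. The check has two parts.

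**1. The definitions side by side**

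*Liver.* Take a recipient who dies on day 3 of a cause that is neither liver failure nor an acute vascular complication.

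- PNF: the death falls within 7 days and outside the vascular exclusion, so it counts.
- Graft survival: there was no retransplant and the death is not attributed to liver failure, so it does not count.

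The two rules disagree for this recipient. Expected PNF numbers are small. With the article's own rates (Sample Size Calculation: 5% HOPE, 10% SCS), they are 55 × 0.05 = 2.75 and 55 × 0.10 = 5.5 per group, so even one or two such deaths would be noticeable.

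*Kidney.* PNF and graft survival both rest on graft loss, and neither names death. They do not conflict. What is open is whether graft loss includes death with a functioning graft. Read literally it does not, and such deaths would be censored.

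**2. Scale, on assumed rates**

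The article gives no 12-month rates for graft failure or for other death. Assume a net graft-failure risk g of 5% or 10%, a net other-death risk d of 2% to 15%, and constant hazards over 12 months. Let a = −ln(1 − g) and b = −ln(1 − d).

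- One minus Kaplan-Meier, other deaths censored: 1 − exp(−a) = g
- Cumulative incidence of graft failure (CIF): a/(a + b) × [1 − exp(−(a + b))]
- All-cause graft failure: 1 − exp(−(a + b))

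Example with g = 10%, d = 15%: a = 0.1054, b = 0.1625, a + b = 0.2679. All-cause failure = 1 − exp(−0.2679) = 23.5%. CIF = (0.1054/0.2679) × 23.5% = 9.24%.

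| g | d | 1 − KM | CIF | All-cause | 55 × CIF | 55 × all-cause |
|---|---|---|---|---|---|---|
| 5% | 2% | 5.0% | 4.95% | 6.90% | 2.72 | 3.80 |
| 5% | 5% | 5.0% | 4.88% | 9.75% | 2.68 | 5.36 |
| 5% | 10% | 5.0% | 4.75% | 14.50% | 2.61 | 7.98 |
| 5% | 15% | 5.0% | 4.62% | 19.25% | 2.54 | 10.59 |
| 10% | 2% | 10.0% | 9.90% | 11.80% | 5.45 | 6.49 |
| 10% | 5% | 10.0% | 9.75% | 14.50% | 5.36 | 7.98 |
| 10% | 10% | 10.0% | 9.50% | 19.00% | 5.22 | 10.45 |
| 10% | 15% | 10.0% | 9.24% | 23.50% | 5.08 | 12.92 |

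- **Estimator effect** (1 − KM minus CIF): at most 10.0 − 9.24 = 0.8 points. If one instead fixes the actual incidences at 10% graft failure and 15% other death, 1 − KM is 10.87%, an excess of 0.9 points, or about half a recipient in 55.
- **Definition effect** (all-cause minus 1 − KM): from 6.90 − 5.0 = 1.9 points to 19.25 − 5.0 = 14.25 points, that is, about 2 to 14.

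Which deaths count therefore matters far more than which estimator is used.

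**The case against.** The strongest reply is that cause-specific graft survival is a legitimate target. It isolates the organ, which is what the perfusion is meant to protect, and the article never calls the outcome all-cause. No death is lost, because patient survival is reported separately and would show deaths that had been attributed away from the graft. Censoring is also not written down. It follows from the event definition and the named method, but the detailed rules may sit in a full protocol or SAP that is not shown. PNF and graft survival need not nest either: a retransplant for an acute vascular complication ends graft survival without being PNF. All of this stands. It limits the point to labelling, estimator and consistency, and does not remove it.

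Several stronger readings are tempting but unsupported:

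- *The PNF conflict covers both organs.* The kidney definitions agree with each other.
- *No kidney death counts.* That is only the literal reading of an undefined term.
- *A large share of graft failures is lost.* On assumed mortality, cause-of-death and retransplant rates, one can calculate that 31% to 62% of failures go uncounted. The inputs are not in the article, and the figure presumes that every death is a graft failure, which is the question at issue.
- *Attribution will favour one arm.* The article does not say who classifies cause of death. Open-label conduct makes such bias possible but does not show it.

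**Conclusion.** The point holds for the liver definition as written. Non-liver-failure deaths can only be censored under the stated method, event status needs a cause-of-death judgement in an open-label trial, and an early non-vascular death not attributed to liver failure is PNF without being a graft-survival event. For kidney the finding is an ambiguity over death with a functioning graft.

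The sizes rest wholly on assumed rates and constant hazards: under about 1 percentage point for the estimator, about 2 to 14 points for the event definition. The article does not show how many recipients would be classified inconsistently. Both outcomes are secondary, and the EAD and DGF analyses are untouched. The change is worth making because it is cheap and removes a real inconsistency, but it does not threaten the trial's main conclusions.

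**What to change.** 1. For each organ, report all-cause graft survival by Kaplan-Meier. The events are retransplant, graft loss or return to dialysis as applicable to the organ, or death from any cause. This measure needs no cause-of-death judgement.
2. Alongside it, report cause-specific graft loss, labelled as such, by the cumulative incidence function with other deaths as a competing event.
3. State whether kidney graft loss includes death with a functioning graft.
4. Reconcile the liver PNF and graft-survival rules, so that it is explicit how a death in the first 7 days is classified under each. Under the all-cause measure every such death is an event, so the wording matters mainly for the cause-specific one.

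The cost is revised wording and one extra analysis; death data are already needed for patient survival. The small downside is that the all-cause measure includes deaths unrelated to the graft, which is why the cause-specific incidence should stand beside it.

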#### Kidney Transplant Secondary Outcomes

Secondary outcomes for kidney recipients are the incidence of PNF, defined as irreversible graft dysfunction with graft loss, which can also be due to rejection or vascular thrombosis; postreperfusion syndrome rate; number of dialyses required in the posttransplant follow-up; LHS; renal function, as measured using creatinine level and estimated glomerular filtration rate, at discharge, 1, 3, and 6 months posttransplant; occurrence of acute rejection events, anastomotic or nonanastomotic ureteral stenosis, or vascular thrombosis within 6 months from the transplant; graft survival, defined as the time from transplant to graft loss or return to dialysis; and patient survival.

### Biomarkers of Oxidative Stress, Inflammation, and Ischemia-Reperfusion Injury

Tissue and perfusate samples are assessed for oxidative stress and metabolic state using reverse transcription polymerase chain reaction (RT-PCR), enzyme-linked immunosorbent assay (ELISA), Luminex technology multiplex assays, and mass spectroscopy analysis. Tissue and perfusate samples are also assessed for the inflammatory markers CD39, CD73, E-selectin, vascular cell adhesion molecule 1, intercellular adhesion molecule 1, hypoxia-inducible factors to tumor necrosis factor-α, interleukin 6, and interleukin 8 using Luminex technology multiplex assays and/or ELISA and RT-PCR.

Specific markers related to renal function and tubular injury, including alpha-1-microglobulin, beta-2-microglobulin, albumin, clusterin, cystatin C, epidermal growth factor, neutrophil gelatinase-associated lipocalin, osteopontin, urinary total protein, trefoil factor 3, hepatocyte growth factor, and macrophage stimulating protein, are measured using Luminex technology multiplex assays and/or ELISA in perfusate and/or ultrafiltrate samples collected before and after ex vivo organ reperfusion.

Adenosine, ATP, adenosine diphosphate, adenosine monophosphate, riboflavin, and succinate levels are measured in tissue, perfusate, ultrafiltrate, and reperfusion fluid using high-performance liquid chromatography.

Finally, miR-21, a small target molecule involved in renal and liver ischemia-reperfusion injury processes, is measured.

